## Abstract

**Background:**

Patients with pituitary tumors often live with lifelong consequences of their disease. Treatment options include surgery, radiotherapy, and medical therapy. Symptoms associated with the tumor or its treatment affect several areas of life. Patients need to adhere to long-term contact with both specialist and general health care providers due to the disease, complex treatments, and associated morbidity. The first year after pituitary surgery constitutes an important time period, with medical evaluations after surgery and decisions on hormonal substitution. The development and evaluation of extended patient support during this time are limited.

**Objective:**

The aim of this study is to evaluate whether support within a person-centered care practice increases wellbeing for patients with pituitary tumors. Our main hypothesis is that the extended support will result in increased psychological wellbeing compared with the support given within standard of care. Secondary objectives are to evaluate whether the extended support, compared with standard care, will result in (1) better health status, (2) less fatigue, (3) higher satisfaction with care, (4) higher self-efficacy, (5) increased person-centered content in care documentation, and (6) sustained patient safety.

**Methods:**

Within a quasiexperimental design, patients diagnosed with a pituitary tumor planned for neurosurgery are consecutively included in a pretest-posttest study performed at a specialist endocrine clinic. The control group receives standard of care after surgery, and the interventional group receives structured patient support for 1 year after surgery based on person-centeredness covering self-management support, accessibility, and continuity. A total of 90 patients are targeted for each group.

**Results:**

Recruitment into the control group was performed between Q3 2015 and Q4 2017. Recruitment into the intervention group started in Q4 2017 and is ongoing until Q4 2020. The study is conducted according to the Declaration of Helsinki, and the protocol has received approval from a regional ethical review board.

**Conclusions:**

This study entails an extensive intervention constructed in collaboration between clinicians, patients, and researchers that acknowledges accessibility, continuity, and self-management support within person-centeredness. The study has the potential to compare standard care to person-centered practice adapted specifically for patients with pituitary tumors and evaluated with a combination of patient-reported outcomes and patient-reported experience measures. Following the results, the person-centered practice may also become a useful model to further develop and explore person-centered care for patients with other rare, lifelong conditions.

**Trial Registration:**

Researchweb.org. https://www.researchweb.org/is/sverige/project/161671

**International Registered Report Identifier (IRRID):**

DERR1-10.2196/17697

## Introduction

### Background

Pituitary tumors occur at any age, but most often occur in persons at the peak of their professional career [1]. The annual incidence of pituitary tumors is approximately 4.0 per 100,000 inhabitants [1-4]. Pituitary tumors can be divided into nonfunctioning tumors (nonfunctioning pituitary adenoma and craniopharyngioma) and hormone-producing adenomas (prolactinomas, Cushing’s disease, and acromegaly). Although they are histologically benign, the tumor itself and its treatment often lead to lifelong hormone deficiencies, obesity, neurocognitive dysfunction, visual field defects, diabetes insipidus, and other adverse effects due to the pituitary gland’s vital regulatory function and its proximity to the hypothalamus and optic chiasm [5,6]. Patients with pituitary tumors therefore have excess morbidity and mortality [1,2,4,7-9]. The tumors are treated with surgery and, in some cases, radiotherapy, while endocrine-active tumors can also be managed with medical therapy [6]. A substantial proportion of patients experience tumor recurrence during their follow-up [10]. Recurrence is associated with excess mortality; disease control is therefore of vital importance for patient outcomes [11].

Pituitary tumors constitute a substantial chronic disease burden for patients, affecting several areas of life [12,13]. Low self-reported health is evident with symptoms such as fatigue, memory and concentration difficulties, sleeping problems, and sexual dysfunction [14,15]. Partners of patients have described a lack of information regarding the disease and its treatment as well as concerns related to changes in relational aspects, social life, and family life [16]. Unemployment is also more common among patients with pituitary disease, and a substantial number of patients report having missed work or not performing to their potential at work due to their illness [17].

The disease, its treatment, and related morbidity necessitate that patients adhere to long-term contact with specialist and general health care providers. There is limited knowledge on how to support patients with pituitary tumors to better cope with their lifelong condition. Andela and colleagues [18] evaluated structured patient and partner group education introduced to patients several years after their diagnosis. The 8-week program showed increased and sustained self-efficacy 6 months after the education program and, to some extent, improved patient mood. However, patients did not report any significant differences in perceived quality of life, symptoms, coping style, or illness perception. A nurse-led, 9-month educational program specifically designed for patients with Cushing’s syndrome showed improvement in health outcomes such as pain, physical activity, and aspects of quality of life [19].

Recent reforms covering health and medical care have highlighted the importance of designing care in collaboration with each patient through participation in decisions, providing explicit information, and determining patients’ preferences and abilities [20,21]. Care based on person-centeredness has been promoted, whereby care providers inquire how patients view their health situation and about their needs, resources, and preferences [22,23]. Person-centeredness focuses on preserving patient autonomy, function, and wellbeing and strives to emphasize patient involvement through equalizing power between health care professionals and patients with the main goal of an enhanced health situation for each patient.

This project focuses on how a nurse-led, person-centered practice with a state-of the-art medical team might be beneficial for patients after surgery for pituitary tumors (Figure 1). To our knowledge, this has not been previously studied. This study is presented according to the SPIRIT statement for reporting study protocols [24].

**Figure 1 figure1:**
[figure not shown]
Person-centered practice: integrating person-centered care and the clinical pathway.

### Study Objectives

The aim of the study is to evaluate whether support within a person-centered care practice increases wellbeing for patients with pituitary tumors. Our main hypothesis is that the extended support will result in increased psychological wellbeing compared with the support given within standard of care. Secondary objectives are to evaluate whether the extended support, compared with standard care, will result in (1) better health status, (2) less fatigue, (3) higher satisfaction with care, (4) higher self-efficacy, (5) increased person-centered content in care documentation, and (6) sustained patient safety.

## Methods

### Study Design

The study utilizes a quasiexperimental design with a nonequivalent control group and a pretest-posttest study design. The study is carried out in two sequential steps: (1) a control group of patients receiving standard care up to 1 year after surgery followed by (2) an interventional group where patients receive extended support within a person-centered practice up to 1 year after surgery.

The study is conducted according to the Declaration of Helsinki. All participants in the study have rights to confidentiality and provide written informed consent [25]. Approval for the protocol has been obtained from the regional ethical review board (approval reference 387-15). Any modifications to study procedures have to be reported as formal amendments to the ethical review board for approval.

### Study Setting

A university clinic in western Sweden constitutes the clinical setting for the study. An inpatient neurosurgical unit, an inpatient endocrine unit following surgery, and an outpatient endocrine unit collectively comprise the patients’ care pathway before and after surgery.

### Study Population

All consecutive patients diagnosed with a pituitary tumor planned for neurosurgery at the study center will be asked to participate in the study. Inclusion criteria are planned neurosurgery and ≥18 years of age. Exclusion criteria comprise health conditions that might restrict understanding of the study or ability to adhere to the protocol (eg, cognitive impairments or drug addiction). The power calculation for estimation of sample size was based on two previous hormonal replacement therapy interventions evaluating improvement in psychological general wellbeing [26,27]. We used a range of d values due to different study designs; based on d=0.3326 (no treatment vs treatment in a crossover design) [27] to d=2.826 (before and after intervention) [26], 64-100 patients are needed in each group to obtain an 80% power with a 95% significance. Considering the different design of the study, 90 patients are targeted in each group, also taking into account a 10% discontinuation rate.

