### Plan for Statistical Analysis

Statistical analysis will include descriptive analysis and comparisons between the control and intervention groups. For numerical data, mean, SD, median, and interquartile range will be calculated. Categorical data will be expressed as proportions (%). Background and clinical characteristics for the two groups will be expressed with descriptive data, and differences will be analyzed with the chi‐squared test, independent samples *t* test, or Mann-Whitney U test. The primary outcome will primarily be evaluated by comparing changes in psychological wellbeing between baseline and 1 year after surgery in the two groups. Parametric or nonparametric tests will be used depending on whether data are normally distributed for the purpose of comparing data between the intervention group and control group. Effects will be described as mean differences with 95% CIs. Data will be analyzed using SPSS software package (IBM Inc, Armonk, NY). The significance level will be set at *P*<.05, and all tests will be two-tailed. Subgroup analyses will be performed based on demographic characteristics and disease and treatment characteristics.

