## Results

Inclusion in the control group receiving standard care was completed from Q3 2015 to Q4 2017 with the number of patients needed to evaluate the primary outcome. Recruitment to the group exposed to the intervention has been ongoing since Q4 2017, and the estimated timepoint for completed recruitment is Q4 2020. Final data collection is expected in Q4 2021.

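### The stated 64-100 patients per group does not follow from the effect sizes it is said to rest on, and 90 per group does not give 80% power at the smaller one

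*Protocol article*

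**What the plan says.** The sample-size justification is in the Study Population section of the protocol article. It names two effect sizes for psychological general wellbeing, from two earlier hormone-replacement interventions. The lower is "based on d=0.3326 (no treatment vs treatment in a crossover design") and the upper is "d=2.826 (before and after intervention"). From these it concludes that "64-100 patients are needed in each group to obtain an 80% power with a 95% significance", and then that "90 patients are targeted in each group, also taking into account a 10% discontinuation rate". The Methods part of the Abstract repeats the target: "A total of 90 patients are targeted for each group".

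The Plan for Statistical Analysis sets the significance level at P<.05, says that "all tests will be two-tailed", and bases the primary analysis on the between-group comparison of change in wellbeing from baseline to 1 year. Study Design confirms that the groups are separate and recruited one after the other. Results reports that control-group inclusion was completed "with the number of patients needed to evaluate the primary outcome".

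**The concern.** The article prints both the inputs and the output of its power calculation, and they do not fit together. The cited effects differ about 8.5-fold, yet the patient numbers attached to them differ by a factor of only 1.56. Both effects are within-patient contrasts by the article's own description, while the planned comparison is between two independent cohorts. The section mentions the difference in design when it settles on 90, but gives no step from the effects to that number.

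This is the only sample-size justification for the primary outcome, and closure of control recruitment is reported by reference to the number needed. If power at the smaller cited effect is well below 80%, a null result could be misread as evidence of no benefit from an adequately powered study.

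**Working it through.** **Inputs**
- Significance level: two-sided 5% (Plan for Statistical Analysis). The wording in Study Population, "to obtain an 80% power with a 95% significance", is read the same way.
- Power: 80% (Study Population).
- Effects: d=0.3326 and d=2.826 (Study Population). Both end in 26, which may be a citation number run into the value, so 0.33 and 2.8 were also tried.
- Comparison: change from baseline to 1 year, two independent groups (Study Design; Plan for Statistical Analysis).
- Target 90 per group, 10% discontinuation: 90 × 0.9 = 81 evaluable.

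**Step 1: attempt to reproduce 64-100**

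The normal approximation for two independent groups is n per group = 2(1.960 + 0.842)²/d² = 15.70/d². The exact figures use the noncentral t.

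| d | n per group, normal | n per group, t |
|---|---|---|
| 0.3326 | 142 | 143 |
| 0.33 | 145 | 146 |
| 2.8 | 3 | 4 |
| 2.826 | 2 | 4 |
| 0.40 | 99 | 100 |
| 0.50 | 63 | 64 |

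Neither end of the stated range comes from a cited effect. Both ends come exactly from d=0.50 and d=0.40, which are not cited. Reading the trailing 26 as a citation does not change this.

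**Step 2: can any single formula give both ends?**

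Required n varies roughly as 1/d². The ratio of the effects is 2.826/0.3326 = 8.5, so n should differ by about 8.5² ≈ 72-fold. The stated ratio is 100/64 = 1.56.

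Other readings of d=0.3326 or 0.33:
- paired test, two-sided: 71-73 (normal) or 73-75 (t);
- two groups, one-sided: 112-115;
- paired test, one-sided: 56-59.

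Two isolated near-matches exist:
- A one-sided paired normal calculation at d=0.33 gives 57, and 57/0.9 rounds up to 64. This contradicts two-tailed testing and the two-group design, and it uses the dropout allowance that the section applies later to reach 90.
- If 2.8 were a misprint for 0.28, a two-sided paired normal calculation gives 101. The same formula gives 73 at d=0.33, not 64.

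**Step 3: power at the planned size**

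The normal approximation is power ≈ Φ(d√(n/2) − 1.960). For n=81 and d=0.3326: 0.3326 × √40.5 = 2.117, and Φ(0.157) = 0.562. The exact t value is 0.557.

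| n per group | Power at d=0.3326 (t) | Smallest d with 80% power (t) |
|---|---|---|
| 64 | 46% | 0.50 |
| 81 | 56% | 0.44 |
| 90 | 60% | 0.42 |
| 100 | 65% | 0.40 |

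At d=0.33 with 81 per group, power is 55%. At d=0.40 with 81, it is 72%.

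**Step 4: sensitivity to the scale of d**

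Step 3 takes d in SD units of the change score. If 0.3326 were instead in raw-score SD units, the effect on the change score would be 0.3326/√(2(1−ρ)), where ρ is the baseline to 1-year correlation. The article gives no ρ, so the values below are assumptions (normal approximation, 81 per group).

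| Assumed ρ | Power, change score |
|---|---|
| 0.3 | 43% |
| 0.5 | 56% |
| 0.6 | 66% |
| 0.7 | 78% |
| 0.8 | 92% |

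On that scale, 81 per group reaches 80% power when 141.9 × 2(1−ρ) ≤ 81, that is ρ of about 0.72 or more. With baseline adjustment by ANCOVA the condition is 141.9 × (1−ρ²) ≤ 81, that is ρ of about 0.66 or more.

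**The case against.** The strongest reply concerns the power figure. If the cited effects are within-patient, then 0.3326 should not be used as a between-group effect to arrive at 56%. On a raw-score scale with a high baseline to 1-year correlation, power at 81 could approach or exceed 80%. This stands as a caveat: the 56% depends on d being in SD units of change. It uses the effect as the plan itself used it, however, and the article states neither a correlation nor an adjustment that would support a better figure. It does nothing to rescue the 64-100.

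A second reply is that 2.8 may be a slip, for example for 0.28, so that the requirement of 4 patients reflects a reporting error and not a design assumption. That is possible, but it is conjecture and still leaves the lower end unexplained. A printed value that is wrong also needs correcting.

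A third reply is that the section offers a range, acknowledges the different designs and chooses a number inside that range, so 81 evaluable is not a contradiction. It is true that 81 lies between 64 and 100. It is nevertheless below the number the section itself attaches to the less favourable end, and the range has no valid derivation.

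Finally, a journal article condenses its full protocol. That would excuse an omitted formula. It does not excuse printed inputs and a printed result that are incompatible.

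**Conclusion.** The concern holds. Under the article's own two-sided 5% level, 80% power and two-group design, the cited effects require 143 (146 at d=0.33) and 4 patients per group, not 64-100. This conclusion does not depend on whether the trailing digits are a citation, and no single formula tried gives both ends.

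Taking d in SD units of the change score, 81 evaluable per group gives 56% power at 0.3326 (60% if all 90 are evaluable). The smallest effect with 80% power is 0.44 SD with 81, or 0.42 SD with 90. The size of the shortfall rests on that choice of scale; the failed derivation does not. The statement needs correcting because it is the sole support for the claimed power on the primary outcome.

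**What to change.** Delete the derivation from d=0.33 to 2.8 in Study Population and replace it with text such as:

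> With 90 patients enrolled per group and 81 evaluable after 10% discontinuation, the study has 80% power (two-sided 5%) to detect a between-group difference of 0.44 SD in PGWB change from baseline to 1 year. Power is 56% for a difference of 0.3326 SD (55% for 0.33 SD).

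The statement in Results about the number needed should then refer to this detectable difference. If the team adopts a baseline-adjusted analysis, it should state the detectable difference for that analysis together with the assumed baseline to 1-year correlation.

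The correction does not change the recruitment target or call for more patients. It costs the rewording of one paragraph and a less favourable power statement.

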### Recruitment

Recruitment is coordinated by a research nurse ([name]) experienced in the care of patients with pituitary tumors and specifically trained in endocrine research studies. Patients who are planned for surgery and are eligible for the study will be contacted by phone about 1 week before surgery to receive information regarding the study. A written description of the study is sent to the patients after this initial contact. The same nurse meets the patient on the day before surgery to inform about the study again. After answering any potential questions regarding the study, patients provide written informed consent. In the case of acute surgery, the neurosurgeon responsible for the patient obtains verbal and written consent before surgery. No study activities are initiated before verbal and written informed consent.

### Patient and Public Involvement

To be able to develop a valid person-centered practice from the patients’ point of view, a group of patients with pituitary tumors who have experienced long-term care participated in the development of the intervention. In two workshops, discussions were held between patients, clinicians, and researchers on current care and specific needs stated by the patients. The expressed preferences in care were integrated into the content of the intervention. Specifically, these preferences included increased accessibility, an identified contact person within care, patient education program early after surgery, relatives included in care, and knowledge of medical treatment, surgery, and tumor recurrence. When results from the study are assessable, efforts will be made to disseminate the results in appropriate forums for patients and their relatives. In addition, the findings of the study will be communicated in peer-reviewed publications in scientific journals, in PhD theses, and at scientific meetings.

### Intervention

The structure and content of the intervention are built on principles for person-centeredness. Within the intervention, repeated patient narratives and continuously revised, documented health care planning ensure that the care is systematically practiced according to principles for person-centeredness (Figure 2). Self-management support*,* being an important component in the intervention, is primarily conducted between the patient and a nurse care manager. Each patient in the intervention is allocated a hospital-initiated nurse care manager, who initiates the first contact with the patient at the inpatient unit before discharge after surgery. The primary goal of the support from the nurse care manager is to facilitate the patient’s own resources in managing illness as well as giving specific health education on, for example, physical activity and diet. Patient-held documentation, the health book, frames the content of self-management support. The health book includes detailed information on the structured clinical care pathway, contact information for the nurse care manager, and preparatory questions that could be used before appointments with the health care team. Questions to encourage reflections on good and bad days and what constitutes or hinders good health are also included in the health book. After each contact between the patient and nurse care manager, a health plan, including agreed goals, is revised. Within the health book, it is also possible for the patient to self-assess and monitor symptoms and health in writing or by drawing. They are also able to reflect and self-assess issues related to work, social support, economy, and other health factors such as physical activity, sleep, sex life, and diet.

**Figure 2 figure2:**
[figure not shown]
Content of the extended support within a person-centered practice until 1 year after surgery.

Other components of the intervention comprise accessibility and continuity*,* which are secured by a structured clinical care pathway (Figure 3). The patient has continuous access to the nurse care manager by telephone and face-to-face contact according to a structured follow-up plan for 1 year after surgery. An interdisciplinary team as well as a patient education program constitute distinct parts of support. The structured clinical care pathway visualizes the care that is preplanned and defines the roles of the different heath care providers. The patient education program at 6-9 months after surgery comprises education for both the patient and their relatives. It is aimed at promoting the development of skills and knowledge needed to self-manage health. The content includes information about surgical treatment, symptoms, and signs as well as issues related to health and quality of life. The patients’ knowledge of diagnosis and surgery is increased by lectures. Discussions during the program are targeted at including common experiences and skills needed to manage different symptoms in daily life. The patient education program also provides requisites for peer support in nonclinical aspects.

To qualify as an outpatient nurse care manager, the nurse must have experience caring for patients with pituitary tumors. Further, it is mandatory to attend a 1-day education course covering updated information on signs and symptoms, hormonal treatments, neurosurgical aspects, person-centered care, health promotion, and the role of the nurse care manager. Each nurse, depending on their experience and needs, completes observation in different care units such as neurosurgery or inpatient care or with specific team members, such as dietitians and physical therapists, included in the patient care pathway. Literature and other materials are made available to the nurse care managers.

